##### Family relations

Three categories of family members are defined: 1) nuclear family, being partner and/or children; 2) family of origin, being parents, brothers and/or sisters; and 3) aunts and female cousins on the family side where breast cancer is prevalent, being the second generation relatives most likely to be affected by genetic testing of the patient. Participants report the frequency of contact with each category of relatives, as well as indicate the quality of their relationship on a scale of 1-10.

##### Family communication

For each above-mentioned relative, participants indicate whether, and if so, when (directly after information, just before DNA-result, after DNA-result) and how often (on a scale of 1-5), they had spoken to this relative about hereditary breast cancer. Also included is the Openness to Discuss Hereditary Cancer in the Family scale (ODHCF) which consists of 7 items each scored 1,2,3,4 with a range 7-24: once for the nuclear family (α = 0.79) and once for the family of origin (α = 0.93) [61].

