### Study outcomes

Participants are asked to fill out a questionnaire twice: at baseline and following the conclusion of genetic counseling and/or testing (follow-up). Some measures are used in both questionnaires, while others are only included in either baseline or follow-up.

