### Secondary outcomes

#### General information (baseline)

##### Demographical and breast cancer information

Data are gathered on age, education level, work status, marital and parental status, cancer status, medical information need (scale 1-10), use of breast cancer information resources and type of information previously given by their referring physician.

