#### Experiences with genetic counseling and testing (follow-up)

##### Choice of procedure

Participants describe reasons for choosing DNA-direct or DNA-intake.

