### Sample size calculation

For this intervention study, participants are not randomized into groups, but given their own choice. This leads to certain complications when it comes to a formal power calculation. First, the ratio between the two procedures is unknown: this may either be balanced (50% versus 50%) or unbalanced (e.g. 20% versus 80%). Second, due to not randomizing, the results will have to be corrected for multiple confounders, which are not all known at this point. The sample size, based on aforementioned ratio between both groups (choice of procedure), needs to be large enough to be able to integrate these confounders into a regression model. Using a power of 80% and a two-tailed probability level for statistical significance testing of 0.05, while taking into account group ratios ranging from balanced (50% versus 50%) versus unbalanced (to an estimated maximum of 20% versus 80%), the total sample size has been set to 150 patients with breast cancer.

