### Statistical analysis

To compare general characteristics, baseline and follow-up results between the intervention versus control group, the unpaired *t*-test will be used for continuous variables, Mann–Whitney *U* test for non-parametric variables and chi-square test for dichotomous variables. For the comparison of baseline versus follow-up results within each group, the paired *t*-test will be used for continuous, Wilcoxon test for non-parametric and McNemar’s test for dichotomous variables. Multivariate analysis will consist of a regression model using the follow-up results as outcome (dependent) variables, to be compared between the intervention versus control groups as independent variables, with the baseline results as covariates supplemented by variables that were found to be statistically significant in previous univariate analyses. The probability level for statistical significance testing is set at 0.05 (two-tailed). The SPSS 18.0 statistical package will be used to analyze the data.

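### Contact frequency, relationship quality and family openness (ODHCF) are measured only at follow-up in self-chosen groups, so the planned adjustment for baseline results cannot be applied to them

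*Protocol article*

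**What the plan says.** All references are to the protocol article.

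- **Two questionnaires.** Everyone completes one at baseline and one after counseling and/or testing. Under Study outcomes: "Some measures are used in both questionnaires, while others are only included in either baseline or follow-up".
- **Timing of the family measures.** Family relations and Family communication both stand under the secondary-outcomes heading that begins "Experiences with genetic counseling and testing (follow-up". The first asks: "Participants report the frequency of contact with each category of relatives, as well as indicate the quality of their relationship on a scale of 1-10". The second covers whether, when and how often each relative was told, and then: "Also included is the Openness to Discuss Hereditary Cancer in the Family scale (ODHCF) which consists of 7 items". The ODHCF is completed twice, once for the nuclear family and once for the family of origin.
- **Baseline content.** The section on demographic and breast cancer information states: "Data are gathered on age, education level, work status, marital and parental status, cancer status". Baseline also holds the empowerment questionnaire, one of whose four factors is Social Support, and the distress, quality-of-life, risk-perception and worry measures. None of these records contact, relationship quality or openness within the family.
- **Allocation and correction.** Under Design, women choose freely between the procedures. Under Sample size calculation, because there is no randomization, "the results will have to be corrected for multiple confounders". Under Statistical analysis, the follow-up result is regressed on group "with the baseline results as covariates supplemented by variables that were found to be statistically significant" in the univariate tests.
- **Role of the outcome.** The Abstract lists family characteristics and determinants of the choice of procedure among the secondary outcomes.

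**The concern.** The plan accepts that self-chosen groups need correction, and its main tool is the baseline value of the same measure. For contact frequency, relationship quality and the ODHCF that value is never collected. If women who choose DNA-direct already come from more (or less) open families, the follow-up comparison will show that difference even when the procedure changes nothing.

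The second cost concerns the analysis of choice. Contact and relationship quality are natural candidates as confounders and as determinants of choice. A rating given after counseling may already have been altered by what happened in between, so it is a poor measure of the state in which the choice was made. The Discussion adds that DNA-intake patients who do not meet the testing criteria are not offered a test, while DNA-direct patients can be tested regardless. The share of women who rate their family after a DNA result can therefore differ between the groups.

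**Working it through.** **No figure in the plan to reproduce.** The article gives a total of 150, 80% power, a two-sided 5% level and group ratios from 50:50 to 20:80. It gives no effect size or SD, and no ODHCF difference or correlation. What follows is an illustration.

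**Inputs from the article.** N = 150, so 75/75 at one extreme and 30/120 at the other; two-sided 5% level.

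**Assumed inputs.** Prior gap between the groups g = 0.3 SD; within-group correlation between baseline and follow-up r = 0.6 to 0.7; procedure effect zero.

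**Step 1. Standard error of the group difference, in SD units.** SE = √(1/n1 + 1/n2).
- 75/75: √(2/75) = 0.163
- 30/120: √(1/30 + 1/120) = 0.204

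**Step 2. Gap seen at follow-up.**
- It shrinks with the correlation: r × g = 0.6 × 0.3 = 0.18 to 0.7 × 0.3 = 0.21 SD
- It persists in full, as for a stable trait: 0.30 SD

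**Step 3. Probability that an unadjusted two-sided 5% t-test rejects** (noncentral t, 148 df, noncentrality = gap/SE).

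| Gap at follow-up | 75/75 | 30/120 |
|---|---|---|
| 0.18 SD | 19% | 14% |
| 0.21 SD | 25% | 18% |
| 0.30 SD | 45% | 31% |

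The nominal rate is 5%.

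**Step 4. What a baseline value would do.** Regression on baseline subtracts about r × g from the observed gap.
- If the gap shrinks: r × g − r × g = 0, so the bias is removed.
- If it persists in full: g − r × g = 0.3 × (1 − r) = 0.12 SD at r = 0.6 and 0.09 SD at r = 0.7. Adjustment cuts the bias from 0.30 SD but does not remove it.

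**Step 5. Precision.** The baseline value removes r² = 0.36 to 0.49 of the variance within groups. This is equivalent to a sample 1/(1 − r²) = 1.56 to 1.96 times as large for that outcome.

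**Step 6. Number of added items.** ODHCF: 7 items × 2 versions = 14. Relations: 3 categories of relatives × 2 items (contact, quality) = 6. Total 20.

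**The case against.** The strongest reply is about weight and wording, and much of it stands.

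- **The outcome is peripheral.** The hypothesis in the Background names distress, satisfaction, and waiting and processing times. The family characteristics in the Abstract could partly mean the pedigree data listed under Other measures. This limits the importance of the point. It does not remove it, because the family measures are listed as secondary outcomes and Statistical analysis compares follow-up results between groups.
- **Adjustment is not wholly absent.** A reader might infer that no planned analysis can separate a procedure effect from prior differences. That goes too far: marital and parental status and the Social Support factor are collected at baseline and could enter the model. They are proxies for another construct, however, not a baseline value of the same scale.
- **Choice driven by openness is not shown.** A reader might take the exclusion of women with family-communication problems, checked at the triage call, as evidence that openness drives the choice. It is not. Those women enter neither group, and nothing links openness to choice among eligible women. The exclusion narrows the range of family differences but does not balance self-chosen groups.
- **Not every rating follows a DNA result.** A reader might assume that all women answer after disclosure. Follow-up comes after counseling and/or testing, and some DNA-intake women are not tested. What holds for all is that the ratings come after the procedure.
- **Measuring once is declared.** Study outcomes says so openly, and questions on when and how often relatives were told do belong at follow-up. This does not supply the covariate for contact, relationship quality and openness.
- **Asking early may change behavior.** A baseline ODHCF could prompt family talks, which the follow-up questionnaire then counts. This is a real downside, though it would apply equally to both groups.

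**Conclusion.** The point holds as a moderate one. As written, the adjustment for baseline results cannot be applied to contact frequency, relationship quality or the ODHCF, and only weak proxies are available. A group difference on these measures may partly reflect who chose DNA-direct, and the ratings are poor candidates as confounders or determinants of choice.

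The size is illustrative. With an assumed prior gap of 0.3 SD and no procedure effect, rejection at 75/75 is about 19-25% if the gap shrinks with r = 0.6 to 0.7 and about 45% if it persists. At 30/120 the figures are 14-18% and 31%. The article gives neither the gap nor the correlation.

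The article does not support the stronger conclusion that the study's judgment on the acceptability of DNA-direct is undermined, since the hypothesis does not rest on these measures. Nor would a baseline value settle the matter: adjustment reduces self-selection bias but does not eliminate it.

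**What to change.** 1. Add the contact-frequency and relationship-quality items and both versions of the ODHCF to the baseline questionnaire.
2. Keep the ODHCF and the communication items (whether, when and how often relatives were told) at follow-up.
3. Adjust the follow-up ODHCF for its baseline value, and use the baseline relationship items as candidate confounders and determinants of choice.
4. Report any remaining group difference as an association, not as an effect of DNA-direct.

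The cost is about 20 short items in a questionnaire that every participant already receives, plus the possibility that asking about openness early prompts family talks, equally in both groups. If that is a concern, add only the six contact and relationship items at baseline and report the ODHCF comparison as descriptive.

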#### Other measures

Waiting and processing times, as well as family pedigree characteristics, are also gathered.

### Sample size calculation

For this intervention study, participants are not randomized into groups, but given their own choice. This leads to certain complications when it comes to a formal power calculation. First, the ratio between the two procedures is unknown: this may either be balanced (50% versus 50%) or unbalanced (e.g. 20% versus 80%). Second, due to not randomizing, the results will have to be corrected for multiple confounders, which are not all known at this point. The sample size, based on aforementioned ratio between both groups (choice of procedure), needs to be large enough to be able to integrate these confounders into a regression model. Using a power of 80% and a two-tailed probability level for statistical significance testing of 0.05, while taking into account group ratios ranging from balanced (50% versus 50%) versus unbalanced (to an estimated maximum of 20% versus 80%), the total sample size has been set to 150 patients with breast cancer.

### Statistical analysis

To compare general characteristics, baseline and follow-up results between the intervention versus control group, the unpaired *t*-test will be used for continuous variables, Mann–Whitney *U* test for non-parametric variables and chi-square test for dichotomous variables. For the comparison of baseline versus follow-up results within each group, the paired *t*-test will be used for continuous, Wilcoxon test for non-parametric and McNemar’s test for dichotomous variables. Multivariate analysis will consist of a regression model using the follow-up results as outcome (dependent) variables, to be compared between the intervention versus control groups as independent variables, with the baseline results as covariates supplemented by variables that were found to be statistically significant in previous univariate analyses. The probability level for statistical significance testing is set at 0.05 (two-tailed). The SPSS 18.0 statistical package will be used to analyze the data.

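### In a self-selected comparison, covariates beyond the baseline results stay only if univariately significant; this can drop real confounders and does not exclude variables that the procedure affects

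*Protocol article*

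**What the plan says.** All references are to the protocol article.

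- **Allocation.** Under Sample size calculation, "participants are not randomized into groups, but given their own choice". The same section accepts the consequence: "the results will have to be corrected for multiple confounders, which are not all known at this point". It allows for splits from 50:50 to 20:80 in a total of 150.
- **Univariate analyses.** The Statistical analysis section opens with tests "To compare general characteristics, baseline and follow-up results between the intervention versus control group", followed by paired tests "For the comparison of baseline versus follow-up results within each group".
- **Model.** The multivariate step is "a regression model using the follow-up results as outcome (dependent) variables", with procedure as the independent variable, "with the baseline results as covariates supplemented by variables that were found to be statistically significant in previous univariate analyses".
- **Level.** "The probability level for statistical significance testing is set at 0.05 (two-tailed").

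The article names no confounders and does not limit the supplementary variables to those fixed before the procedure.

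**The concern.** Without randomisation, the procedure effect is only as credible as the adjustment. Whether a variable confounds depends on its relation to both choice and outcome. A between-group p-value below 0.05 reflects the imbalance together with the sample size and the split, and says nothing about the outcome. In a study of 150, and more so with a 20:80 split, a moderate imbalance in a strong predictor can miss 0.05 and leave the model.

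Three features raise the stakes:

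- The hypothesis in the Background is that DNA-direct does not increase distress and gives equal satisfaction. Residual confounding can create a spurious difference. It can also mask a real increase in distress, which is the more consequential error here.
- Decisional conflict and satisfaction are collected only at follow-up. They have no baseline value of their own in the model, so they lean more heavily on the supplementary covariates.
- The tests that feed the rule include follow-up results. Waiting time, for example, is meant to differ between procedures. As a covariate it could absorb part of the effect under study.

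**Working it through.** **Inputs from the document.** N = 150; splits 50:50 (75/75) and 20:80 (30/120); selection and testing at 0.05 two-tailed; baseline results always in the model. Imbalances and confounder strengths are assumptions, because the document gives none.

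**The plan's own figure.** N = 150 cannot be reproduced, because the article states no effect size; it is taken as given. Solving for 80% power as a scale: d = (1.960 + 0.842) × √(1/n₁ + 1/n₂), which is 2.802 × 0.1633 = 0.46 SD at 75/75 and 2.802 × 0.2041 = 0.57 SD at 30/120.

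**Step 1: chance that a real imbalance passes the screen.** The unpaired t-test has noncentrality d / √(1/n₁ + 1/n₂) and critical value 1.976 on 148 degrees of freedom. For d = 0.3 the noncentrality is 0.3/0.2041 = 1.47 at 30/120 and 0.3/0.1633 = 1.84 at 75/75.

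| True imbalance | Kept at 30/120 | Kept at 75/75 |
|---|---|---|
| 0.2 SD | 16% | 23% |
| 0.3 SD | 31% | 45% |
| 0.4 SD | 49% | 68% |
| 0.5 SD | 68% | 86% |

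A confounder imbalanced by 0.3 SD is more likely to be dropped than kept at either split.

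**Step 2: what this does to the estimate.** Simulation with no true procedure effect and the baseline score always in the model (coefficient 0.5). Each confounder is imbalanced by 0.3 SD and shifts the outcome by 0.2 per SD. Ranges cover both splits and different residual variances.

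| Scenario | Bias (SD) | Type I error |
|---|---|---|
| Five confounders, same direction, between-group screen | 0.10–0.13 | about 8–11% |
| As above, confounders also correlated with the baseline score | 0.07–0.08 | 6–7% |
| Two confounders, or three one way and two the other, between-group screen | about 0.02–0.06 | about 5–7% |
| Screen keeps variables significant against group or outcome | about 0.01–0.05 | about 5% |
| Five confounders, all forced in | about 0 | about 5% |

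For the first row, with no confounder adjusted for, the bias would be 5 × 0.3 × 0.2 = 0.30 SD. The screen removes more than half of that, because it tends to keep a confounder in the samples where its imbalance is largest. The remaining 0.10–0.13 SD is roughly a fifth of the difference that the study could detect with 80% power (0.10/0.46 = 0.22; 0.13/0.57 = 0.23).

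**Step 3: a variable that the procedure changes.** Assume a group difference of 0.8 SD in that variable, a coefficient of 0.4 on the outcome and a direct effect of 0.1. The total effect is 0.1 + 0.8 × 0.4 = 0.42. The variable passes the screen in 98–99.8% of runs, and the estimate then falls from about 0.42 to about 0.10 SD. This shows what the wording would permit; it does not predict what the analysts will do.

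**The case against.** **Baseline results enter regardless.** A reader might infer that every confounder must pass the significance test. It need not: the screen governs only what supplements the baseline results. Those may mean the outcome's own baseline value or all baseline measures; on the wider reading, GHQ-12, IES and empowerment are already forced in. This stands and narrows the point. The general characteristics, which the section names separately from baseline results, remain under the screen. For the same reason, it goes too far to say that adjustment of decisional conflict and satisfaction depends wholly on the rule.

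**Follow-up results are the outcomes.** The same sentence gives follow-up results the role of dependent variables. A reader might infer that the plan intends to adjust for consequences of the procedure. The document does not say so. What stands is that the wording does not exclude it.

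**The harm can be small.** The largest figures need five confounders acting in one direction and unrelated to the baseline score. A single confounder with 0.3 SD imbalance and coefficient 0.3 leaves a bias of 0.03–0.05 SD and a type I error of 4.7–5.9%. This stands, so a range must be given. Screening on association with the outcome alone would not fully remove the problem in the five-confounder case (bias 0.05–0.08 SD), and the section describes only between-group and within-group tests.

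**Confounders are not all known.** That explains why a complete list is impossible. It does not justify choosing among the variables already collected by p-value.

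**An article condenses the full protocol.** That would answer a complaint about missing detail. Here the rule itself is stated.

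**Conclusion.** The point holds in a limited form. The section fixes a significance-based rule for supplementary covariates in a comparison that the article itself says must be corrected for confounding. At N = 150 the rule can drop real confounders: the chance of keeping one imbalanced by 0.3–0.4 SD is 31–49% at 30/120 and 45–68% at 75/75. Those figures rest only on the stated sample size, splits and level, for a confounder of the assumed size.

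The resulting bias and error rate rest on assumptions about the number, strength and direction of the confounders and on how the screen is applied. They run from near nominal to 0.13 SD and about 11%. The upper end should not be quoted alone. The possible entry of variables that the procedure affects is an ambiguity to close, not a planned error.

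**What to change.** Change the covariate sentence in the Statistical analysis section before the outcomes are analysed:

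1. Replace the significance rule with a short fixed list of pre-procedure covariates, kept in every between-group model whatever their p-value. Candidates already collected are age, education, parental status, cancer status, information need, empowerment score, baseline GHQ-12 and baseline IES. Rank them in advance and size the list to the smaller arm.
2. State that no variable that the procedure can affect may be a covariate. Do not word this as a bar on anything measured after the choice. Family history forms reach DNA-direct patients in the package sent after they choose (Intervention), and the baseline questionnaire is given at inclusion without its order relative to the choice being stated (Recruitment).
3. Name the adjusted estimate, not the unpaired test, as the main between-group result.
4. Do not adjust for DNA-test result among tested patients in the main model. The Discussion says that DNA-intake patients who do not meet the testing criteria are not offered the test, whereas DNA-direct patients can be tested regardless, so who is tested differs by arm.

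The cost is wording and some degrees of freedom, with no new data. The loss is more noticeable if one arm has only about 30 patients, which is why the list should be short.
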